### Sample size and power calculation

A reduction in pain of at least 10 mm on a 0–100 mm visual analogue scale is deemed a clinical significant improvement. Due to the three study arms of our RCT, there are also three null hypotheses tested:| A - B | ≥ 10 | A - C | ≥ 10 and | B - C | ≥ 10 points on the VAS pain scale, according to a superiority design. In which A, B and C stands for dextrose, autologous blood and perforation only respectively. A number of 47 patients is required in each trial arm when a two-sided 98% confidence interval is used, with a two-sided alpha of 2%, corresponding to a z-value of 2.34 (J Scott Armstrong: Tables for Statistical Significance with Multiple Comparions). To adjust for a maximum of 10% dropout over the one year follow up period, 55 patients will be included in each of the three trial arms. Therefore, a total of 165 patients are needed. It is expected that each week in both hospitals a total of 3 patients can be included. Therefore, the inclusion period takes about 55 weeks. Patients that are withdrawn from the study will not be replaced, since there is accounted for these dropouts in the power analysis.

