**Methods/design:**

A multicenter, randomized controlled trial with a superiority design and 12 months follow-up will be conducted in four Dutch hospitals. One hundred sixty five patients will be recruited in the age of 18 to 65 years, with chronic symptomatic lateral epicondylitis lasting longer than 6 weeks, which have concordant pain during physical examination. Patients will be randomized by block randomization to one of the three treatment arms. The treatment will be blinded for patients and outcome assessors. The following three injection therapies are compared: perforation with application of autologous blood, perforation with application of dextrose and perforation only. Injections will be performed ultrasound guided in a standardized and automated way. The primary endpoint is: pain (change in ‘Visual Analogue Scale’). Secondary endpoints are quality of life and functional recovery. These measurements are collected at baseline, 8 weeks, 5 months and 1 year after treatment.

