Besides the effectiveness of the injectables, the hypothesis is that the needle is used to either break up scars or poke holes in the injured tendon so that bleeding occurs. The blood cells carry precursors, which eventually develop into collagen to replace the damaged tendon. Therefore, this study compares the different injectables with perforation without application of an injectable.

The current debate on studies related to injectables for LE is that in most cases the perforations are performed manually and ‘blindly’ without ultrasound guidance. Moreover, the number and depth of perforations is often not defined. Proper comparison of injectables for LE is therefore questionable [7]. The proposed study compares the effectiveness of perforation of the Extensor Carpi Radialis Brevis (ECRB) tendon to perforation with application of autologous blood or dextrose in the treatment of LE in a standardized and ultra-sound guided way. This overcomes bias due to manually performed injection therapy.

Our hypothesis is that there is no difference in effectiveness between perforation only and perforation with application of one of the injection fluids. The potential health care efficiency gain consists of more homogeneity in the treatment of LE. Hereby, unnecessary treatments can be avoided, a more universal method of treatment can be established and the quality of the treatment can be improved.

The primary objective of this study is to compare the difference in effectiveness of perforation only versus perforation with application of autologous blood or dextrose on pain in the treatment of LE. The primary endpoint is pain on the lateral side of the elbow after a provocation test 5 months after treatment. The secondary objectives are to examine quality of life and functional recovery.

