## Methods/design

### Study design

This trial is a multicenter, blinded, three-arm randomized controlled trail with a superiority design with a 12 months follow-up. Data will be presented in line with the CONSORT statement.

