### Statistical analysis

To compare groups the three groups (A – B, A – C and B - C) Chi-square tests will be used for categorical variables, and independent t-tests for continuous variables. The primary aim is to assess whether the reduction in pain for perforation with application of autologous blood or dextrose is more than 10 points compared to perforation only.

If so, a comparison will be made between the reduction in pain for perforation with application of autologous blood versus dextrose. A mean and a two-sided 98% confidence interval will be calculated. A mixed model will be used taking into account effects of time and treatment. The analyses are primarily performed according to the intention-to-treat principle.

In detail, data will be analyzed in the per protocol (pp) set as well as in the intention-to-treat (itt) set of patients. The pp-set consists of all patients, categorized according to the treatment eventually received, with non-missing observations on the pain VAS at all three visits during follow-up (8 weeks, 5 months and 1 year). The itt-set consists of all randomized patients.

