To get a better understanding, a linear mixed model analysis will be performed with the three repeated measurements of pain VAS as dependent variables. Along with treatment (a three-level nominal variable) the following covariables will be included in the model as independent variables: baseline pain VAS, the binary variable perceived aggravation of pain due to work ((totally) agree vs otherwise) and a three-level nominal variable time (visit number). Moreover, the interaction between treatment and time will be tested. If this interaction is not significant at the 0.01 level, then one overall treatment effect will be estimated assuming parallelism of the treatment effect. If this interaction turned out to be significant at the 0.01 level, then the effect of the 5 months’ visit will be considered the main effect of interest. Effects will be quantified by estimating two-sided 98% confidence intervals of the pair wise mean differences in pain VAS between the three treatment groups. Equivalence between two treatments is accepted if such a confidence interval is totally overlapped by the interval − 10 + 10. A restricted maximum likelihood estimation method will be used to estimate the coefficients so that missing values are properly imputed in order to meet the itt-condition. Under the pp-condition only patients with non-missing observations will enter the linear mixed model.

Similar analysis will be performed for functional recovery and quality of life. Otherwise the descriptives of the secondary outcome measures will be reported for the three groups.

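### The design is labelled superiority, but its nulls and only confidence-interval rule are those of equivalence, its primary aim is a gain of more than 10 points, and nothing says which governs

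*Protocol article*

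**What the plan says.** All places are in the protocol article.

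- **Label.** The abstract describes "A multicenter, randomized controlled trial with a superiority design and 12 months follow-up", and Study design repeats it: "three-arm randomized controlled trail with a superiority design with a 12 months follow-up".
- **Expectation.** Background: "Our hypothesis is that there is no difference in effectiveness between perforation only and perforation with application of one of the injection fluids". The stated benefit is that unnecessary treatment can be avoided.
- **Null hypotheses.** Sample size and power calculation gives three nulls, one per pair of arms (A dextrose, B autologous blood, C perforation only), each an absolute difference of at least 10, ending "and | B - C | ≥ 10 points on the VAS pain scale, according to a superiority design". It gives 47 per arm, a two-sided alpha of 2% with z = 2.34, and 55 per arm after dropout. It gives no SD and no power.
- **Primary aim.** Statistical analysis: to assess "whether the reduction in pain for perforation with application of autologous blood or dextrose is more than 10 points compared to perforation only". The next step is conditional: "If so, a comparison will be made between the reduction in pain for perforation with application of autologous blood versus dextrose".
- **Decision rule.** The mixed-model paragraph of the same section estimates two-sided 98% intervals for the pairwise differences between the three groups, then states: "Equivalence between two treatments is accepted if such a confidence interval is totally overlapped by the interval" from −10 to +10. It states no other interval-based rule.

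**The concern.** These statements describe three different tests. A superiority label implies a null of zero difference. The printed nulls and the ±10 rule are those of an equivalence test. The primary aim is superiority by a margin of 10, and the text does not say whether the estimate or the confidence limit must pass 10.

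The condition placed on blood versus dextrose adds a further conflict. The sample-size section lists that pair as one of three hypotheses of equal standing, and the mixed-model paragraph estimates it without any condition.

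At stake is what counts as a positive trial. The message the authors expect to give, that the fluids add nothing to perforation, can be supported only by the equivalence rule. Under the superiority label and the primary aim, the same data would be a failed trial, and a failed superiority aim could then be reported as no difference without equivalence having been shown.

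**Working it through.** **1. Does the stated 47 reveal the design?** It cannot be reproduced, because SD and power are missing. Solving backwards for the SD, with a difference or margin of 10 and z = 2.326 (two-sided 2%):

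- Superiority against zero: SD = 10·√(47/2) / (2.326 + z_power). This gives 48.48/3.168 = 15.3 at 80% power and 48.48/3.608 = 13.4 at 90%.
- Equivalence, margin ±10, true difference 0: SD = 10·√(47/2) / (2.326 + z_(1−β/2)). This gives 48.48/3.608 = 13.4 at 80% and 48.48/3.971 = 12.2 at 90%.

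An SD of 13.4 fits both superiority at 90% power and equivalence at 80%, so 47 does not show which design was sized. The stated z of 2.34 in place of 2.326 moves these SDs by less than 0.1. The dropout step is not the issue: 47/0.9 = 52.2, so 53, and 55 covers it.

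**2. What the rules say about the same result.** The SD is assumed (15, 20 and 25 mm). The half-width of the 98% CI is 2.326·SD·√(2/47), which is 7.2, 9.6 and 12.0 mm. A positive difference favours the fluid. The first three rows use SD 15.

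| Observed difference (98% CI) | Differs from 0 | More than 10, on estimate | More than 10, on limit | Equivalent within ±10 |
|---|---|---|---|---|
| 1 (−6.2 to 8.2) | no | no | no | yes |
| 5 (−2.2 to 12.2) | no | no | no | no |
| 12 (4.8 to 19.2) | yes | yes | no | no |
| 5 (1 to 9) | yes | no | no | yes |

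Row 1 fails the primary aim and meets the equivalence rule. Row 2 fails everything, and is the result most open to being reported as no difference. Row 3 meets or fails the primary aim depending on an unstated choice. Row 4 needs a half-width below 5, so an effective SD below 5/(2.326·√(2/47)) = 10.4 at 47 per arm, or 11.3 at 55.

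**3. How demanding the primary aim is if read on the confidence limit.** P(lower limit > 10) = Φ((d − 10)/SE − 2.326), with SE = SD·√(2/47) = 3.09 at SD 15 and 4.13 at SD 20:

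- true 10 mm: 1%
- true 15 mm, SD 15: 24%
- true 20 mm: 82% at SD 15, 54% at SD 20

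**4. Power under equivalence.** With true difference 0, power = 2Φ(10/SE − 2.326) − 1, or zero where this is negative. At 47 per arm:

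- SD 15: 2Φ(0.906) − 1 = 64%
- SD 20: 2Φ(0.098) − 1 = 8%
- SD 25: zero, because the half-width of 12.0 exceeds the margin

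With all 55 analysed, the figures are 76%, 23% and zero. At SD 15, 80% power needs 2·(15·3.608/10)² = 58.6, so 59 per arm before dropout, against 2·(15·3.168/10)² = 45.2, so 46, for superiority against zero.

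**The case against.** The strongest defence is that the nulls are a slip, with the alternative printed as the null, and that a hierarchy can be inferred: one aim is called primary, and the mixed model is introduced as giving further insight. That reading is possible, and 47 per arm is compatible with it. It does not settle the matter. The ±10 equivalence rule and the expectation of no difference would still stand against a primary aim of more than 10 points, and the hierarchy is never stated. Nor is this detail that an article may leave to an analysis plan: the statements are printed and they disagree.

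Four stronger readings are tempting, and the documents do not support them.

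- **That one result can give flatly opposite verdicts.** A CI inside ±10 rules out an estimate or a limit above 10, so the equivalence rule and the primary aim cannot both be met. Row 1 is a failed aim and a shown equivalence, which agree in substance. Only a CI lying wholly between 0 and 10 is both superior to zero and equivalent. That needs an effective SD below about 10.4, outside the 15 to 25 assumed here, though baseline adjustment and pooling of visits could lower the effective SD. Moreover, no zero-difference decision rule is written; it is implied by the label and the listed t-tests.
- **That blood versus dextrose would never be tested.** Statistical analysis opens by listing all three pairs, and the mixed model estimates every pairwise interval without a condition. The condition contradicts those lines; it does not remove the comparison.
- **That equivalence could be invented after the data are seen.** Margin, interval level and acceptance rule are all prespecified. What is not prespecified is which rule carries the conclusion.
- **That changing the wording settles everything.** Step 4 of the working shows that the sample-size basis must be revisited too.

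**Conclusion.** The point holds as a contradiction in the governing hypothesis. The label says superiority, the nulls and the only interval rule say equivalence, the primary aim says superiority by 10 points on an unspecified quantity, and the condition on blood versus dextrose conflicts with both the three hypotheses and the unconditional pairwise intervals. The same result can therefore be positive, negative or inconclusive according to the rule applied.

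The contradiction rests on the text alone. The sizes rest on an assumed SD and on a simple two-sample comparison without baseline adjustment. Because it leaves the primary conclusion undefined, it must be corrected before unblinding.

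**What to change.** Before unblinding, name one governing framework and make the label, null and alternative, primary aim and decision rule agree.

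**If equivalence**, which fits the Background expectation, the printed nulls and the ±10 rule:

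- Relabel the design as equivalence with a margin of ±10 mm. Remove the aim of more than 10 points and the condition on blood versus dextrose.
- Report all three pairwise 98% CIs of the 5-month difference.
- CI inside ±10: conclude equivalence. If it also excludes 0, report a difference smaller than the relevant margin.
- CI wholly beyond +10 or wholly below −10: conclude a relevant difference.
- Any other CI: equivalence not shown.
- State that a non-significant difference is not evidence of equivalence.

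**If superiority**, restate the nulls as a difference of 0, or as a gain of at most 10 tested on the confidence limit, and make the ±10 equivalence rule secondary.

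In either case, state the SD and power behind 47 per arm for the chosen framework.

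The cost is an amendment to the protocol and analysis plan, plus a fresh sample-size justification. It should not be described as free of consequences for numbers: under equivalence the power may prove less favourable, for example 59 per arm before dropout for 80% power at SD 15, against the 55 planned with dropout included.

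### The null hypotheses and the only interval rule are those of an equivalence trial, the label and primary aim are those of a superiority trial, and the plan does not settle which decides

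*Protocol article*

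**What the plan says.** Superiority is the declared design in three places of the protocol article. The abstract has "randomized controlled trial with a superiority design and 12 months follow-up", the study design section has "with a superiority design with a 12 months follow-up", and the sample size section attaches the label to the hypotheses themselves.

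Those hypotheses (Sample size and power calculation) are three nulls, one per pair of arms. Each states that the absolute difference is 10 or more; the last reads "B - C | ≥ 10 points on the VAS pain scale, according to a superiority design". The same section gives a two-sided alpha of 2%, a z-value of 2.34, a 98% confidence interval and 47 patients per arm. It gives no SD and no power.

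The Background states the expectation: "Our hypothesis is that there is no difference in effectiveness between perforation only and perforation with application of one of the injection fluids".

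The Statistical analysis section then says two things:

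- "The primary aim is to assess whether the reduction in pain for perforation with application of autologous blood or dextrose is more than 10 points" better than perforation only. If that is shown, the two injectables are compared with each other. Pairwise t-tests and a 98% interval are planned, but no decision rule is attached to the interval.
- In the linear mixed model, which is introduced as an aid to understanding, pairwise 98% intervals are read by this rule: "Equivalence between two treatments is accepted if such a confidence interval is totally overlapped by the interval" from −10 to +10.

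**The concern.** A null hypothesis is what the data are asked to refute. Refuting an absolute difference of 10 or more establishes that two arms differ by less than 10. That is the conclusion of an equivalence trial. A superiority trial refutes no difference or, if it must show a benefit beyond a margin, a benefit of at most that margin. The sample size section joins the first kind of null to the second kind of label in one sentence. The analysis section repeats the split, with a superiority aim and an equivalence rule.

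What is at stake is what the trial may report as its primary result. A finding that rejects the stated null is a failure against the stated aim. If the framework is left open, it can be chosen after the results are known.

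**Working it through.** **1. Possible results set against the three statements.** Take the 98% interval for the extra pain reduction of an injectable over perforation only.

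| 98% interval | Stated null (absolute difference ≥ 10) | Primary aim (benefit above 10) | ±10 rule |
|---|---|---|---|
| Wholly inside −10 to +10 | Rejected | Not met | Equivalent |
| Wholly above +10 | Not rejected | Met | Not equivalent |
| Excludes 0, contains +10 | Not rejected | Met only if excluding 0 is enough | Not equivalent |
| Contains 0 and extends beyond ±10 | Not rejected | Not met | No verdict named |

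The first two rows show the contradiction. The result that rejects the stated null fails the aim, and the result that most clearly meets the aim leaves the null standing. The third row shows that the aim itself does not say whether the interval must exclude 0 or 10.

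**2. Can 47 per arm settle which framework was meant?** The figure can be neither reproduced nor refuted, because SD and power are missing. It can be inverted under an assumed power.

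Inputs from the sample size section: n = 47 per arm, 10 mm, two-sided 2% (exact z = 2.326). Assumptions: power of 80% or 90%, and an unadjusted comparison of two means, so SE = SD × √(2/47) = 0.2063 × SD.

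- Difference test at a true 10 mm: SD = 10 / [(2.326 + z_power) × 0.2063].
  - 80%: 10 / (3.168 × 0.2063) = 15.3
  - 90%: 10 / (3.608 × 0.2063) = 13.4
- Equivalence with margin 10 and true difference 0: SD = 10 / [(2.326 + z_(1+power)/2) × 0.2063].
  - 80%: 10 / (3.608 × 0.2063) = 13.4
  - 90%: 10 / (3.971 × 0.2063) = 12.2

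With the plan's z of 2.34, the 80% values are 15.2 and 13.4. Both frameworks can yield 47 from SDs of similar size, so the number does not show which was intended.

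**3. Why the choice changes what 47 delivers.** At an assumed SD of 15.2, SE = 3.14.

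- Power to detect 10 mm: Φ(10/3.14 − 2.326) = 81%.
- Power for equivalence of truly equal arms, one pair: 2 × 0.806 − 1 = 61%. For 80%, 61 per arm would be needed.
- If superiority means that the interval must exclude 10, the 81% applies to a true difference of 20 mm.

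**4. Error control per pair.**

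- For a zero-difference null, a 98% interval wrongly excludes 0 in 2% of trials.
- At a true difference of 10, equivalence requires the estimate to lie below 10 − 2.326 × SE. The chance of this is at most Φ(−2.326) = 1%.

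**5. Can one interval both exclude 0 and lie inside ±10?** Its half-width must be below 5, so SD < 5 / (2.326 × 0.2063) = 10.4 at 47 per arm.

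**The case against.** The best defence is that null and alternative were swapped in one line. The z-value is taken from tables of significance for multiple comparisons, which suits pairwise difference tests. The analysis section names its aim as primary, compares the injectables with each other only if that aim is met, and presents the mixed model as supplementary. Expecting no difference is also compatible with running a superiority test. This makes a superiority reading plausible. It does not remove the contradiction: the nulls would still be wrong as written, and the only rule that turns an interval into a verdict would still serve the other framework.

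Four stronger readings are tempting, and the documents do not support them.

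- *That the 2% alpha guards against the wrong error.* Step 4 shows that the same interval limits both errors for each pair.
- *That one result supports opposite clinical conclusions.* An interval inside ±10 says under either framework that the injectable is not more than 10 points better. What changes is whether the trial counts as positive. The sharper clash, different from zero and also equivalent, needs an SD below about 10.4.
- *That a non-significant t-test will be reported as no difference.* The plan nowhere says so, and its equivalence rule requires more.
- *That this is really an equivalence trial and 47 was computed for it.* Nothing in the article ties 47 to either test.

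The power figures also ignore baseline adjustment and repeated measurements, both of which are in the mixed model and could narrow the interval.

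**Conclusion.** The point holds as a contradiction between stated elements: the nulls and the ±10 rule against the superiority label and the aim of more than 10 points. It is not a matter of detail left to an analysis plan, because the article states all four and they do not fit together. The order of the analysis section leans towards superiority but does not settle the question.

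The contradiction needs no numerical assumption. The size attached to it does: at 80% power, 47 per arm implies an SD of about 15.3 mm for a 10 mm difference test and about 13.4 mm for equivalence of equal arms. The power, the true difference and the unadjusted two-sample comparison are assumptions here, so these figures show only that 47 has no single meaning. They do not show that the trial is underpowered.

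**What to change.** Before analysis, the sponsor should name one primary framework and bring the abstract, Study design, Sample size and power calculation, and Statistical analysis into line with it.

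- *If superiority:* correct the three nulls, state whether the 98% interval must exclude 0 or 10, and label the ±10 equivalence rule as secondary.
- *If equivalence:* change the design label and the primary-aim sentence, and make the ±10 rule primary.

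In either case:

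- give one verdict rule for each pairwise 98% interval, including an inconclusive outcome;
- state that a non-significant t-test is not evidence of no difference;
- report the SD, power and test from which 47 was actually derived, and restate the power if 47 was derived for the other framework.

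The cost is wording, with no new data collection. The restated power may be less favourable than a reader would now assume.
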